## Abstract

**Background::**

Optimal extent of lymph node dissection for colon cancer is debatable. Extensive lymphadenectomy may increase complication rate, while limited lymph node dissection may compromise oncological outcome. One of promising ways to find balance is to tailor extent of lymph node dissection to patient’s individual anatomy using ICG lymphatic mapping.

**Methods::**

This is a single center interventional phase II trial with single group assignment aiming to determine if ICG lymphatic mapping sensitivity is sufficient to guide resection margins selection in colon cancer surgery. The trial’s primary endpoint is proportion of pN+ patients in which affected lymph nodes are detected only within margins of ICG spread. Sample size of 101 patients was calculated using Buderer method ^[19]^ with a confidence level (1 − *α*) of 0.95 as a minimum of cases required to test accuracy of lCG lymphatic mapping for estimated sensitivity of 0.99 and precision of 0.03. The average of pN+ cases in our center (42%) was used as prevalence. Secondary endpoints are incidence of adverse events related to ICG lymphatic mapping, feasibility of ICG lymphatic mapping for colon cancer, incidence of lymph node metastases outside conventional resection margins (10 cm), colon cancer lymphatic spread patterns, proportion of operations which extent is affected by ICG lymphatic mapping. The trial is conducted among female or male patients, 18 years or older, with signed informed consent, and diagnosed primary colon cancer. Inclusion criteria include pathologically confirmed adenocarcinoma of the colon, T1-4aN0-2bM0-1b, clinical indications to colonic resection, ECOG – 0–2. Exclusion criteria consist of acute bowel obstruction, bleeding or perforation, adjacent organ invasion or peritoneal carcinomatosis, and contraindications to ICG administration. Eligible patients are allocated for colonic resection with intraoperative ICG mapping. During pathological examination, lymph nodes are assessed for presence of metastases and location in relation to tumor and fluorescence margins. The study began on 26 July 2022 and is conducted in and financed by N.N. Petrov NMRC of Oncology in Saint Petersburg, Russia, it is conducted in.

**Results::**

If after 101 ICG lymphatic mapping procedures, sensitivity of >96% is observed, this will provide rationale behind tailoring resection margins to fit ICG spread.

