**Figure 3. F3:**
[figure not shown]
Example of specimen marking (sigmoid resection). Tags are attached to the specimen according to Japanese classification of lymphatic node groups^[15]^. Segments of D1 collector are named according to Japanese Classification of pericolic lymphatic collector groups^[16]^. IO and IA marks are borders of D1 ICG spread visualized during surgical procedure. So, the area of ICG fluorescence is projected on lymphatic node groups harvested during surgery.

**Table 2 T2:** Protocol synopsis

Title	ICG fluorescence guided lymph node mapping for determination of bowel resection margins in colon cancer
Study design	Patients with primary resectable colon cancer are assigned for colonic resection with intraoperative ICG lymphatic mapping. The dye’s mesenteric distribution is marked by surgeon on the specimen. During pathological examination each lymph node is assessed both for presence of metastases and for its exact location in relation to primary tumor and margins of indocyanine distribution.
Aims and endpoints	*Aim of the study:*
	To determine if ICG lymphatic mapping sensitivity is sufficient to guide resection margins selection in colon cancer surgery by comparing lymphatic distribution of subserosally injected dye to the actual spread of lymphatic metastases reported by pathologists after specimen examination.
	*Primary endpoint:*
	Proportion of pN+ patients with affected lymph nodes detected only within margins of ICG distribution.
	*Secondary endpoints:*
	incidence of adverse events related to ICG lymphatic mapping; feasibility of ICG lymphatic mapping for colon cancer (proportion of ICG spillage affecting interpretation); incidence of lymph node metastases outside conventional resection margins (10 cm); colon cancer lymphatic spread patterns; proportion of operations which extent is effected by ICG lymphatic mapping.
Patients	Female and male patients 18 years or older with signed informed consent and diagnosed primary colon cancer T1-4aN0-2bM0-1b
Number of patients	101
Study duration	The study is conducted starting from 26 July 2022, until target number of patients is enrolled
Estimated time until target number of patients is reached	2 years
Statistical analysis	If after 101 ICG lymphatic mapping procedures we record sensitivity of 96% or higher, it will mean that this method might be considered as a reliable tool to visualize locoregional lymphatics of a colon segment affected by a tumor.

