### Sample size calculation and statistical analysis

As the study is aimed to access if ICG mapping can be used to reliably define resection margins in colon cancer surgery, a case of affected lymph nodes only within fluorescence margins was regarded as a true positive case, no fluorescence in pN0 – true negative, pN+ because of metastatic lymph nodes outside fluorescence zone – false negative, pN0 despite presence of fluorescence – false positive.

Sample size of 101 patients was calculated using Buderer method^[19]^ with a confidence level (1 – *α*) of 0.95 as a minimum of cases required to test accuracy of lCG lymphatic mapping for estimated sensitivity of 0.99 and precision (margin of error) of 0.03. This resulted in sensitivity threshold of 0.96. The calculation was performed for minimum acceptable kappa (k0) of 0.6, expected kappa (k1) 0.9. The resultant estimated power (1 – *β*) is 0.96. The average of pN+ cases in our center (42%) was used as prevalence – proportion of outcome (p).

For statistical analysis of primary endpoint, sensitivity will be calculated according to standard formula (number of true positive cases divided by sum of true positive and false negative cases) and its meaning will be compared to the estimated 0.99 ± 0.03. For analytical purposes other measures of accuracy will be calculated as well.

“Intent-to-treat” analysis will be performed, thus once enrolled patients are to be analyzed, irrespective of received treatment. To focus on specificities ICG spread regardless of influence of patients with treatment deviations and those with unsuccessful ICG injection, “per-protocol” analysis will be performed as well.

For secondary endpoints type of analysis will depend on nature of the data. Descriptive statistics will be used to depict feasibility of ICG lymphatic mapping, incidence of adverse events, incidence of lymph node metastases outside conventional resection margins and proportion of operations which extent is affected by ICG lymphatic mapping. Lymph node metastases pattern will be assessed as calculation of frequency of affected nodes related to number of studied nodes in each group. Parametric and non-parametric criteria will be used to compare mean values and contingency tables.

In cases of missing data, should more than 10% of data be missing, the variable will be deleted, because estimates are likely to be biased^[20]^. In other situations multiple imputations will be used.

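### The 0.96 success mark is the lower edge of a planned precision interval but is applied to the observed sensitivity without a confidence bound, so with about 42 pN+ patients a pass screens out roughly 0.89 and cannot show 0.96

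*Protocol article*

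**What the plan says.** The success rule appears in three places in the protocol article.

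- Abstract, Results: "If after 101 ICG lymphatic mapping procedures, sensitivity of >96% is observed, this will provide rationale behind tailoring resection margins to fit ICG spread".
- Table 2 (protocol synopsis), Statistical analysis row: "If after 101 ICG lymphatic mapping procedures we record sensitivity of 96% or higher", after which the method is described, in hedged terms, as possibly a reliable way to visualise the regional lymphatics.
- Sample size calculation and statistical analysis: sensitivity is true positives over true positives plus false negatives, and "its meaning will be compared to the estimated 0.99 ± 0.03".

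The last section also shows where 0.96 comes from. The sample size was set "for estimated sensitivity of 0.99 and precision (margin of error) of 0.03", followed by "This resulted in sensitivity threshold of 0.96". The Endpoints section restricts the denominator of the primary endpoint to pN+ patients. None of these places attaches a confidence limit, a null value or a type I error to the observed sensitivity.

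**The concern.** A margin of error describes how far an estimate may lie from the truth. Subtracting it from the expected value gives the planned lower edge of an interval around 0.99. If 0.96 is the lowest sensitivity the trial wants to stand behind, it is the confidence limit that should clear it. The protocol asks only that the point estimate clear it, so the uncertainty for which the trial was sized plays no part in the decision.

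The error that matters is a pass when too many patients have metastatic nodes outside the fluorescent zone, because the Abstract links a pass to tailoring resection to that zone. Readers need to know which values of true sensitivity a pass rules out, and the protocol does not tell them.

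**Working it through.** **Inputs** (all from Sample size calculation and statistical analysis): assumed sensitivity 0.99; margin of error 0.03; confidence 0.95, taken as two-sided (z = 1.96) because that reproduces the stated size; pN+ prevalence 0.42; 101 patients.

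**1. The plan's own figure.** Buderer: pN+ needed = 1.96² × 0.99 × 0.01 / 0.03² = 42.26. Total = 42.26 / 0.42 = 100.6, rounded up to 101. The sample size reproduces. Threshold: 0.99 − 0.03 = 0.96.

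**2. What the rule means in patients.** Expected pN+ = 101 × 0.42 = 42.4 (95% binomial range 33 to 52). At 42: 41/42 = 0.976 passes and 40/42 = 0.952 fails, so at most one false negative is allowed. The same holds for 33 to 49 pN+. From 51 upward two are allowed (49/51 = 0.961). At exactly 50 the answer depends on the wording, since 48/50 = 0.96.

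**3. Chance of passing.** For true sensitivity S and 42 pN+: P(pass) = S^42 + 42 × (1 − S) × S^41. For S = 0.96 this is 0.180 + 0.315 = 0.495. The last column averages over a Binomial(101, 0.42) pN+ count, using the strict operator.

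| True sensitivity | P(pass), 42 pN+ | P(pass), random pN+ count |
|---|---|---|
| 0.99 | 0.934 | 0.936 |
| 0.98 | 0.795 | 0.802 |
| 0.96 | 0.495 | 0.507 |
| 0.95 | 0.372 | 0.384 |
| 0.92 | 0.140 | 0.150 |
| 0.90 | 0.068 | 0.075 |
| 0.89 | 0.046 | – |

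At a true sensitivity of 0.96, P(pass) lies between about 0.40 and 0.67 over 33 to 52 pN+.

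**4. What a passing result supports (Clopper-Pearson lower limits).**

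| Result | Two-sided 95% | One-sided 95% |
|---|---|---|
| 41/42 | 0.874 | 0.892 |
| 42/42 | 0.916 | 0.931 |

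With no false negatives the two-sided limit is 0.025^(1/n): 0.894 at n = 33 and 0.932 at n = 52. A perfect 42/42 has one-sided p = 0.96^42 = 0.18 against 0.96. Wilson and Jeffreys limits for 42/42 also stay below 0.96 (two-sided 0.916 and 0.942). Only the Wald interval exceeds it, because its width collapses to zero.

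**5. What excluding 0.96 would take.** With no false negatives, 0.96^n ≤ 0.05 needs n = 74 pN+ (74 / 0.42, about 177 patients), and 0.96^n ≤ 0.025 needs n = 91 (about 217 patients). The chance of 74 or more pN+ among 101 patients is about 2 × 10⁻¹⁰.

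**The case against.** **This is a phase II screen, and a decent one.** Any cut-off on a point estimate passes about half the time when the truth equals the cut-off. That is an error only if 0.96 is the value to be excluded, and the protocol sets no null for sensitivity. As a screen, the rule passes 0.99 with probability 0.93 and 0.89 with probability 0.046. This stands, and it is why the point concerns what a pass may be said to show. It does not make the rule useless.

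**The protocol hedges.** Table 2 speaks only of what might be considered, and the Abstract's Conclusions ask for more data. A reader might infer that the protocol claims a pass proves a sensitivity of at least 0.96, or that resections would be reduced on the 96% rule alone. The documents support neither. The passage on reducing resection, in Objectives and study hypothesis, rests on a different condition: no affected nodes beyond the ICG margin in a subgroup.

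**The worst case is an extreme.** A reader might take the 0.874 limit to mean that a passing method would probably miss nodes in about 1 in 8 pN+ patients. At a true sensitivity of 0.874 the trial passes only about 2.5% of the time (2.9% with a random pN+ count). It marks the edge of what a pass leaves open.

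**An analysis plan may supply an interval.** It may, and a missing interval alone would be no finding. But the trigger is already stated on the point estimate, and an interval reported beside it would not change that.

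**Power is given as 0.96.** The protocol ties that figure to kappa of 0.6 versus 0.9. It reproduces as a kappa goodness-of-fit power (0.961 at 101 patients, prevalence 0.42, two-sided 0.05) and says nothing about sensitivity against 0.96.

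**Two details are minor.** The comparison range reaches 0.99 + 0.03 = 1.02, which is approximation shorthand; only its lower side is used. The operator mismatch moves P(pass) at 0.96 only from 0.507 to 0.514.

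**Conclusion.** The point holds as a fault in the decision rule. The sample size arithmetic is correct. A precision-derived lower edge has become a cut-off for the observed value, and at about 42 pN+ patients that rule cannot show that sensitivity is at least 0.96, whatever the result. A pass excludes only sensitivities below about 0.87 (one false negative) to 0.92 (none).

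This should be fixed, but it does not undermine the trial: the rule discriminates well between 0.99 and about 0.89, and the stated conclusions are cautious. The figures assume 42% pN+, all 101 patients evaluable, independent patients and exact binomial limits. The protocol sets no error level for this decision, so both one-sided and two-sided limits are shown; neither reaches 0.96.

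**What to change.** 1. Make the primary result sensitivity with a Clopper-Pearson 95% interval at the realised pN+ count, and base the conclusion on its lower limit. Let this replace the comparison with 0.99 ± 0.03.
2. Choose one of two courses before the results are seen:
   - Keep the 96% point-estimate rule, labelled a phase II screen. State that at 42 pN+ a pass excludes only sensitivities below about 0.87 (one false negative) to 0.92 (none), that with no false negatives the limit runs from 0.89 to 0.93 over 33 to 52 pN+, and that a pass supports a confirmatory study.
   - State an attainable lower-limit criterion. At 42 pN+ nothing above 0.916 can be met. Anything above 0.874 requires zero false negatives, which a true sensitivity of 0.99 achieves with probability 0.99^42 = 0.66.
3. Print the pass probabilities beside the rule, and say nowhere that a pass establishes 0.96.
4. Use one operator in the Abstract and Table 2.

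The cost is wording and one exact interval. No extra patients are needed. The downside is a less favourable conclusion from the same data.

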## Introduction

### Background and rational

Navigational surgery including mapping and tailoring of resection margins can be a solution to the major problem of colon cancer surgery: finding “the least possible not to compromise oncological safety” resection clearance for each patient. Mentioned concept has already been discussed^[1,2]^. But although the idea that all patients are different and therefore require different approaches sounds reasonable, this notion has not met sufficient response because yet there is no tool with proven effectiveness to implement it.

However, there is a lot of evidence on ICG fluorescent imaging for visualization of locoregional lymphatic paths of colonic lesions^[2,3]^, which can guide tailoring. ICG was firstly implemented as a sentinel lymph node detection (SLND) tool but was found to lack accuracy and standardization. Ankersmit *et al* analyzed 8 studies describing 227 SLN procedures in a meta-analysis in 2019 and observed low pooled sensitivity of 63%, negative predictive value 81% and detection rate of 94%^[4]^. The same year Villegas-Tovar *et al* reported similar findings in another meta-analysis of ICG SLND accuracy for colon cancer: they calculated detection rate of 91% (80–98%), sensitivity of 64.3% (51–76%), and specificity of 65% (36–85%) – and concluded that overall ICG performance for detection of lymph node metastases is poor^[5]^. So, it was shown that ICG does help to visualize lymphatics, but it does not work for SLND in colon cancer.

Moreover, assessment of fluorescence and fluorescent lymph node harvest are affected by multiple factors. In particular, 2023 systematic review and meta-analysis of 58 prospective designed studies by Lucas *et al* showed that injection time had a significant impact on aberrant drainage detection favoring preoperative tracer injection^[6]^. The same year Kinoshita *et al* in their series of 56 cases observed both cases with metastatic lymph nodes only in the area along the ICG-stained vascular pedicles and lymph node metastasis in areas along the ICG-unstained vascular pedicles^[7]^.

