### Objectives and study hypothesis

In this trial it is investigated whether the zone of lymphatics’ fluorescence visualized after subserosal ICG injection reflects the region of metastatic spread from a colon segment affected by a tumor. Even though it is assumed that ICG fills in the whole regional lymphatic collector (with all affected nodes), hypothetically, ICG mapping procedure might lead to one of six scenarios (Fig. 1): ICG spreads within conventional resection margins (affected lymph nodes within/outside fluorescence zone), or ICG spreads beyond conventional resection margins (affected lymph nodes within fluorescence zone and within/beyond conventional resection margins), or ICG spreads beyond conventional resection margins (affected lymph nodes outside fluorescence zone and within/beyond conventional resection margins). So, these groups’ detection and analysis will help to make important assumptions and considerations regarding role of ICG lymphatic mapping in colon cancer surgery. For instance, if no affected lymph nodes are observed beyond margins of ICG spread in subcategory of patients with fluorescent zone smaller than conventional resection margins, it will mean that extent of colon and mesentery resection plan can be decreased to fit ICG spread. And on the contrary, if frequency of lymph node metastases beyond ICG spread margins makes method’s sensitivity suboptimal, efficacy of ICG lymphatic mapping will have to be reconsidered.

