### Trial design

#### Design

This is an interventional phase II trial with single group assignment investigating feasibility of defining colon resection margins for colon cancer with ICG by comparing lymphatic distribution of subserosally injected dye with actual spread of lymphatic metastases reported by pathologists after specimen examination.

This is a single center trial. To ensure adherence to the protocol and to avoid logistical and monitoring issues stemming from multicenter design, all patients are enrolled in one center. The study includes ICG lymphatic mapping procedure and extensive pathological evaluation of the specimen, which are not routinely performed in majority of centers. Also, the calculated sample size of 101 is a number of patients, which is possible to enroll in a single center during reasonable time period. So, the risks of type II error, methodological error leading to bias and contradicting results issue, resulting from single center approach were acknowledged and study protocol created to possibly minimize them and ensure that the statistical hypothesis is tested.

Since the main focus of the study is investigation of ICG lymphatic mapping feasibility and currently there is no gold standard of lymphatic mapping for colon, no control group was included.

After signing an informed consent and undergoing screening procedure eligible patients are assigned for colonic resection with ICG lymphatic mapping. The fluorescence is assessed before specimen removal (Fig. 2) and its mesenteric distribution is marked by surgeon on the specimen (Fig. 3). During pathological examination each lymph node is assessed both for presence of metastases and for its exact location in relation to margins of ICG distribution (each lymphatic node is classified according to Japanese classification of lymphatic node groups^[15]^; D1 nodes are also classified according to their distance from primary tumor^[16]^). All screening, intraoperative, postoperative, and pathological data is recorded for further analysis. Protocol synopsis is presented in Table 2.

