#### Endpoints

Primary endpoint
Proportion of pN+ patients in which affected lymph nodes are detected only within margins of ICG distribution (number of patients with affected lymph nodes located within ICG distribution margins divided by the number of all patients with pN+).

Secondary endpoints
Incidence of adverse events related to ICG lymphatic mapping (time frame: 30 days after operation);feasibility of ICG lymphatic mapping for colon cancer (proportion of cases with ICG spillage affecting interpretation);incidence of lymph node metastases outside conventional resection margins – 10 cm (proportion of patients with aberrant lymphatics leading to affected lymph nodes);colon cancer lymphatic spread pattern (descriptive data on incidence of D1, D2 and D3 lymphatic collector metastases and frequencies of D1 collector metastases depending on distance from primary tumor);proportion of operations which extent is effected by ICG lymphatic mapping (number of patients with change of operation plan due to mapping results divided by the number of patients).

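### Pooled ICG containment above 96% is read as a rationale for tailoring margins, although the rule neither limits zone size nor compares with the 10 cm margins

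*Protocol article*

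**What the plan says.** All references are to the protocol article.

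- **Decision rule.** Abstract, Results: "If after 101 ICG lymphatic mapping procedures, sensitivity of >96% is observed", then "this will provide rationale behind tailoring resection margins to fit ICG spread". Table 2 (Statistical analysis) uses the same single criterion, "If after 101 ICG lymphatic mapping procedures we record sensitivity of 96% or higher", but concludes only that the method may be reliable for visualising the regional lymphatics.
- **What is computed.** Endpoints defines the primary endpoint as pN+ patients whose affected nodes lie inside the ICG margins, over all pN+ patients. Sample size calculation and statistical analysis computes it as the "number of true positive cases divided by sum of true positive and false negative cases" and compares it with 0.99 ± 0.03.
- **Purpose.** The Introduction describes the problem as finding the clearance that is "the least possible not to compromise oncological safety".
- **Scenarios.** Objectives and study hypothesis sets out six combinations of ICG spread, node position and conventional margins, among them "ICG spreads beyond conventional resection margins (affected lymph nodes within fluorescence zone and within/beyond conventional resection margins". It links a smaller resection to finding no affected node beyond the ICG spread in patients whose zone is smaller than the conventional margins.
- **Comparator.** Design explains that because "currently there is no gold standard of lymphatic mapping for colon, no control group was included".
- **Secondary endpoints.** Metastases outside 10 cm and operations changed by mapping are both listed, for descriptive analysis.

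**The concern.** The stated problem has two sides: remove enough tissue, and no more than needed. Containment measures only the first. If a given zone is enlarged, a patient already counted as contained stays contained, so the proportion can rise but not fall. Nothing else in the rule offsets this. Even the false-positive definition (any fluorescence in a pN0 patient) is at patient level and does not depend on how wide the zone is.

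A conclusion about tailoring margins to ICG implies that ICG is a better guide than the margins now used, or that it can safely replace them in one direction. The pooled figure addresses neither. It does not show whether the 10 cm margins would have held the same metastases. It also mixes patients with zones smaller than the conventional margins, who inform a reduction, with patients whose zones extend beyond them, who inform an extension. A pass could therefore be cited for a change in either direction without evidence specific to that direction.

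**Working it through.** **1. Reproduce the sample size.** Inputs from Sample size calculation and statistical analysis: sensitivity 0.99, precision 0.03, 95% confidence (z = 1.96), pN+ prevalence 0.42.

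n(pN+) = 1.96² × 0.99 × 0.01 / 0.03² = 42.26; N = 42.26 / 0.42 = 100.6, rounded up to 101. The stated figure reproduces. Expected pN+ patients: 101 × 0.42 = 42.4, so about 42.

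**2. Where the bar falls.** 42/42 = 100% and 41/42 = 97.6% pass; 40/42 = 95.2% fails. The rule therefore allows one pN+ patient with a node outside the zone. The Abstract's strict inequality and Table 2's inclusive one give the same verdict at 42.

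**3. Can a map that adds nothing pass?** Take a map that covers the 10 cm field but misses every metastasis beyond it, all other metastases being inside both. The protocol gives no rate for metastases beyond 10 cm, so let q be the assumed share of pN+ patients with such a node. Then

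P(pass) = (1 − q)^42 + 42 q (1 − q)^41

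| q (assumed) | 0% | 1% | 2% | 3% | 4% | 5% |
|---|---|---|---|---|---|---|
| P(pass) | 1.00 | 0.93 | 0.80 | 0.64 | 0.50 | 0.37 |

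Letting the pN+ count vary as Binomial(101, 0.42) changes these by at most about 0.02. The plain 10 cm margins, scored the same way, have exactly the same probabilities, because they fail in the same patients. At one such patient both score 41/42 = 97.6%.

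**4. Can pooling hide a failure in the small-zone group?** Assume 32 patients with zones extending beyond the conventional margins, all contained, and 10 with smaller zones, 9 contained. Pooled: (32 + 9)/42 = 97.6%, a pass under the Abstract. Small-zone stratum: 9/10 = 90%, with one affected node beyond the zone, so the condition in Objectives and study hypothesis is not met. The same data satisfy one section and fail the other.

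**5. Precision of such a stratum.** The exact 95% interval for 9/10 has a lower limit p solving 10p⁹(1 − p) + p¹⁰ = 0.025, giving p = 0.555, and an upper limit 0.975^(1/10) = 0.997. Even 10/10 has a lower limit of only 0.025^(1/10) = 0.69.

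**6. Expected discordant patients.** At q = 1% to 5%, 42 × 0.01 = 0.4 to 42 × 0.05 = 2.1 patients have a node beyond 10 cm.

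**The case against.** Most of the cross-classification is already intended. The six scenarios cross ICG spread with node position and conventional margins, and the protocol says it will analyse these groups. Metastases beyond 10 cm and changed operations are named secondary endpoints. A single-arm phase II study whose stated aim is whether sensitivity is sufficient may reasonably keep a single primary proportion. Table 2 is already cautious, and the Abstract speaks only of a rationale and adds that more data are needed. This stands as a reason not to change the primary endpoint. It does not repair the Abstract, where the tailoring conclusion follows from the pooled figure alone and none of the planned breakdowns enters it.

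A paired comparison with 10 cm also has real limits. Pathology sees only resected tissue, and the surgeon decides the extent, so where a specimen stops at 10 cm the conventional margins score as contained by construction. Distance classes are stated only for D1 nodes. Few discordant patients are expected. This stands too, and it means the comparison can be descriptive only.

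Two stronger readings are tempting and should be resisted.

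- *Any map wider than 10 cm passes automatically.* It does not. The scenarios include spread beyond the conventional margins with affected nodes outside fluorescence, and two such patients among 42 would fail the rule. The statement holds only for a zone that encloses the affected nodes.
- *The trial would endorse wider surgery.* Tailoring runs both ways, and the protocol's own worked example is a smaller resection. The plan changes cited in the Introduction (16.7% and 23.5%) are given without direction, so they cannot be counted as added tissue.

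**Conclusion.** The concern holds for the conclusion drawn in the Abstract, not for the choice of sensitivity as primary endpoint or for the sample size, which is correct on its own inputs. Passing shows that the ICG zone contained the affected nodes in nearly all pN+ patients. It does not show that ICG is a better guide than 10 cm: a map that adds nothing to the conventional field passes with probability 0.93 to 0.37 when 1% to 5% of pN+ patients have a node beyond 10 cm, and the 10 cm margins would do equally well. Those rates, the 41/42 count for the 10 cm margins and the 32/10 split are assumptions, and the calculation takes 42 pN+ patients.

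A reader might also infer that a control arm is needed. The documents do not support that: each node is located relative to both the tumour and the ICG margins, so the gap lies in what the conclusion rests on, not in the data collected.

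**What to change.** Keep sensitivity as the primary endpoint and report two things with it, in the same pN+ patients:

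1. Containment with an exact confidence interval, separately for patients whose zone is smaller than the conventional margins and for those whose zone extends beyond them.
2. A descriptive cross-table of all metastases inside the ICG zone (yes/no) by all metastases inside 10 cm (yes/no), with the discordant counts. Restrict it to pericolic (D1) nodes, where distance is recorded and the ICG borders are tagged, and note that unresected tissue is not verified.

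Reconcile the Abstract with Objectives and study hypothesis and with Table 2. Pooled containment should support only the statement that ICG outlines the region of nodal spread. Any statement about narrower or wider margins should rest on the matching stratum or on the discordant counts.

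The cost is two short tables from data already recorded and a narrower concluding sentence. The downside is small strata with wide intervals, few discordant patients, and a less favourable headline if the discordant counts are near zero.
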